## Abstract

**Background:**

Physical activity plays a critical role in health, including for effective weight maintenance, but adherence to guidelines is often poor. Similarly, although debate continues over whether a “best” diet exists for weight control, meta-analyses suggest little difference in outcomes between diets differing markedly in macronutrient composition, particularly over the longer-term. Thus a more important question is how best to encourage adherence to appropriate lifestyle change. While brief support is effective, it has on-going cost implications. While self-monitoring (weight, diet, physical activity) is a cornerstone of effective weight management, little formal evaluation of the role that self-monitoring technology can play in enhancing adherence to change has occurred to date. People who eat in response to hunger have improved weight control, yet how best to train individuals to recognise when true physical hunger occurs and to limit consumption to those times, requires further study.

**Methods/design:**

SWIFT (Support strategies for Whole-food diets, Intermittent Fasting, and Training) is a two-year randomised controlled trial in 250 overweight (body mass index of 27 or greater) adults that will examine different ways of supporting people to make appropriate changes to diet and exercise habits for long-term weight control. Participants will be randomised to one of five intervention groups: control, brief support (monthly weigh-ins and meeting), app (use of MyFitnessPal with limited support), daily self-weighing (with brief monthly feedback), or hunger training (four-week programme which trains individuals to only eat when physically hungry) for 24 months. Outcome assessments include weight, waist circumference, body composition (dual-energy x-ray absorptiometry), inflammatory markers, blood lipids, adiponectin and ghrelin, blood pressure, diet (3-day diet records), physical activity (accelerometry) and aerobic fitness, and eating behaviour. SWIFT is powered to detect clinically important differences of 4 kg in body weight and 5 cm in waist circumference. Our pragmatic trial also allows participants to choose one of several dietary (Mediterranean, modified Paleo, intermittent fasting) and exercise (current recommendations, high-intensity interval training) approaches before being randomised to a support strategy.

**Discussion:**

SWIFT will compare four different ways of supporting overweight adults to lose weight while following a diet and exercise plan of their choice, an aspect we believe will enhance adherence and thus success with weight management.

**Trial registration:**

Australian and New Zealand Clinical Trials Registry ACTRN12615000010594. Registered 8^th^ January 2015.

## Background

Overweight and obesity affect almost two-thirds of New Zealand adults and rates continue to climb in some ethnic and demographic groups [1]. The inability of many individuals to lose significant weight by themselves or for most to keep it off is due to a myriad of factors including making changes to lifestyle that are too drastic and therefore not sustainable, the widespread availability of energy-dense foods and sedentary past-times, changes to work and leisure-time energy expenditure, and insufficient support structures [2, 3]. However, considerable debate and confusion also exists in both lay and scientific literature regarding whether there is an “optimal” dietary composition for weight loss [4]. Low-carbohydrate diets in particular have long been purported to have metabolic and clinical advantages over other dietary patterns [5–7]. It makes mechanistic sense that lower carbohydrate diets *could* promote greater weight loss, principally because of a reduction in insulin levels reducing the storage of body fat [8]. However, at the practical level, recent meta-analyses suggest little difference in weight and health outcomes between diets differing quite markedly in macronutrient composition, particularly over time frames longer than 6 months [9–13]. Instead, a far more relevant factor appears to be the degree of *adherence* to the prescribed diet [11, 14, 15], an aspect that is insufficiently measured [16].

Such findings have led expert groups to recommend that the most suitable diets are not those that include a specific nutrient composition per se, but rather ones that entail moderate energy restriction which participants are willing and able to follow long-term [17]. It is becoming clear that several acceptable dietary patterns that differ quite markedly in terms of macronutrient composition are suitable for weight loss. The more important question then becomes how best to encourage and support long-term compliance with one, or more, of these patterns [18]. However, while adherence to dietary change is viewed as a cornerstone of non-communicable disease prevention and management [19], little practical guidance is available identifying which specific factors enhance adherence to dietary advice [3]. The short-term nature of most studies, marked differences in terms of how adherence is assessed, and overall low trial quality limits firm conclusions being drawn about the most efficacious factors [3].

Strong social support is considered an important adjunct to successful weight loss or maintenance [20]. The use of personalised support with nutrition and activity specialists is known to be effective [21], however it is expensive and rarely accessed. Alternative forms of low-intensity but regular support, delivered by non-specialists can result in similar benefits, at a fraction of the cost [22]. Brief monthly support, such as is found in many commercial weight loss programmes, also appears to maintain weight loss better over 2–3 years than other forms of support including interactive websites and self-directed control [23]. However, because such support cannot continue indefinitely, and ongoing development of innovative technology, determining the efficacy of other, low-cost strategies is currently of great interest [24].

Self-monitoring of weight, food intake and/or activity levels has been shown to be one of the most effective strategies employed for successful weight management [25]. However, monitoring of food and activity is time-consuming and adherence dramatically declines over time [26]. The advent of mobile “apps” may offer a more effective way of monitoring food/ activity patterns due to instant feedback of a wealth of information [27]. While self-monitoring strategies are a common component of the myriad of commercially available apps [24], whether they are effective at encouraging behaviour change has rarely been examined, despite their widespread use [28]. Although the top five self-monitoring apps each have a user base of more than 10 million people [28], only one appears to have been tested in a clinical trial [29]. Laing et al. [29] recently demonstrated that use of MyFitnessPal alone, with no accompanying dietary or exercise advice, did not produce significant weight change over 6 months in comparison with usual care. The apparent lack of effect may be due in part to the sharp declines in adherence to app use after the first month [29]. Perhaps this is not surprising given that the response of individuals to self-monitoring can vary considerably, ranging from the “well-disciplined” who endorse this approach, to those that have “diminished support”, where other co-existing factors take precedence [30].

Compared with monitoring of diet or activity, monitoring of body weight is both straightforward and quick. Although weekly or monthly weighing has traditionally been recommended, observational studies suggest that daily weighing may promote weight loss better than less frequent weighing [31–33]. However, few studies have examined the efficacy of daily self-weighing in comparison to less frequent weighing via randomised controlled trials. Steinberg et al. [34] reported a weight loss of 6.6 % over a 6-month period in the daily weighing group compared with only 0.4 % in wait-list controls. It may be that more frequent weighing offers further advantages; Oshima et al. [35] demonstrated that twice-daily weighing resulted in greater weight loss than once-daily weighing in a small group of overweight adults. How these changes related to changes in actual body composition is unknown, but important given that it is widely acknowledged that fat loss, rather than weight loss, provides the key health benefits [36]. Whether such frequent weighing produces adverse psychosocial effects is a matter of concern. However, the limited data to date suggest that no adverse effects, and potentially even some benefits, have been observed, at least over 6–18 months [37–39].

One of the major barriers to effective weight management is that we eat for a variety of complex and interrelated reasons other than hunger, including taste, social interaction and emotional cues. Observational studies demonstrate that many environmental and situational cues influence our eating [40], but those who eat in response to hunger, recognise satiety signals, and give themselves unconditional permission to eat foods of their choosing (intuitive eaters), are more likely to be a healthy weight than those who do not [41, 42]. While people can be trained to eat more intuitively (in response to hunger and satiety), whether this increases weight loss relative to other techniques remains uncertain [43, 44]. An alternative type of *hunger training* has been suggested, where subjects are trained over a few weeks to identify actual (physiological) hunger by connecting the physical feelings of hunger with blood glucose levels [45]. This training has been shown in one small study to produce significant weight loss compared with a conventional approach which required constant dietary restraint [46]. Whether this approach is a viable way of training individuals to eat to their appetites requires further examination, particularly in terms of its ability to work over longer time frames.

Testing the effectiveness of different support strategies should theoretically occur with all participants following the same diet. However, we know that one of the major difficulties in trials which randomise people to follow specific dietary patterns is that any particular diet cannot possibly suit every individual, which undoubtedly influences adherence. Behavioural choice theory posits that outcomes are improved when participants receive the treatment they prefer [47]. It thus seems feasible that tailoring a diet on the basis of individual personal and cultural preferences (i.e. choice) may therefore have the best chance for long-term success [48], perhaps through enthusiasm, a better fit with their overall lifestyle, or supporting personal autonomy. However, whether choice of intervention group versus randomisation affects adherence and outcomes in weight loss studies has been examined infrequently, and the findings do not generally support the theory [49]. There was no evidence of a difference in outcomes from having a preference for a certain intervention in terms of group versus individual treatment [50], low fat versus low carbohydrate diets [51], or choice of commercial diet programme [52]. The remaining study found significantly greater weight loss in those randomised to a diet than in those who were allowed to choose a diet, although clinically important weight losses were observed in both groups [53]. However, many of these studies were relatively small and were unable to provide precise estimates of effects [50, 52, 53], or lasted less than one year [50]. Thus further examination of the impact of being able to *choose* which diet or activity plan to follow is warranted, particularly given the high drop-out rates typically observed in randomised controlled trials of dietary interventions. This is particularly true given under real-world conditions, people seeking to lose weight select their own dietary and/or physical activity approach(es). Moreover, in reality, switching between weight loss strategies will occur even when a particular approach has been suggested by a health professional or within randomised trials.

Two promising and popular dietary approaches, despite relatively little research around their use in humans, include paleolithic diets and intermittent fasting. Paleolithic diets are based on evolutionary principles and include meat, fruit, vegetables and nuts/seeds while eschewing grains, dairy, and processed foods. Early small studies have provided encouraging results [54–56]. However, whether overweight adults can adhere to paleolithic-type diets in the longer-term requires study. Intermittent fasting is usually defined as normal food intake 3–5 days a week and dramatically reduced intake (down to 2 MJ from typical intake of 8–10 MJ) for 2–4 days. Anecdotally this is believed to be much easier than reducing energy intake by a smaller amount (usually 2 MJ/day) *every* day, which forms part of the current guidelines. While a wealth of animal data supports the effectiveness of intermittent fasting for weight control [57], research in humans is less certain [58]. However, the small amount of data available does show modest evidence of effectiveness for treatment of obesity and cardioprotection [59, 60].

Exercise produces more successful weight loss than dietary change alone [61, 62], seems particularly important for weight maintenance [63] and has many additional health benefits, over and above that relating to energy balance. Regular physical exercise is associated with an approximate halving in the risk of cardiovascular disease [64], can decrease the incidence of diabetes by up to 50 % as part of lifestyle counselling [65], and even decrease insulin resistance in those with established metabolic syndrome [66]. However, a major public health challenge is how best to encourage people to be physically active on a regular basis. Although evidence that regular physical exercise is beneficial is overwhelming [67], adherence remains a major issue [68], with lack of time often cited as a major barrier [69]. Thus there has been increasing interest in ascertaining the minimum amount of exercise required that might produce effective health benefits. An alternative to meeting moderate to vigorous physical activity (MVPA) guidelines may be the promotion of high intensity interval training (HIIT). In HIIT, brief periods of high-intensity exercise are interposed with recovery periods at a much lower intensity [70]. Although HIIT regimes typically include 10 minutes or so of intense exercise performed three times per week, as little as 3 minutes of intense exercise per week has been shown to produce cardiovascular and metabolic improvements [71, 72], although effects on body composition are less certain [73]. Although HIIT holds promise, virtually all research to date has been conducted in the laboratory and it is uncertain whether these findings will translate into community settings. If people cannot complete HIIT by themselves, its efficacy as a public health approach is very limited. Whether participants can adhere to a HIIT training regime long-term is also not currently known.

### Aims and objectives

The goal of our study is to determine whether allowing participants to choose from a selection of appropriate diet and exercise plans, within the context of a randomised controlled trial evaluating four different support strategies, enhances adherence and promotes greater weight loss and positive health outcomes. Giving people the choice of which diet and exercise regime is best incorporated into their particular lifestyle is expected to improve adherence, reflects real-world conditions, and is consistent with the lack of evidence for meaningful differences between diet modalities. Acknowledging this concept in conjunction with testing different support strategies offers a unique opportunity to determine how best to support individuals to make dietary and exercise changes under real-world conditions.

The primary aim of our study is to determine the effectiveness of different support strategies (control condition, brief support, daily self-weighing, app use, hunger training) on weight loss at 12 and 24 months. Secondary aims are to determine:(i)the effect of different support strategies on body composition, dietary intake, exercise, inflammatory markers, blood lipids and lipoproteins, adiponectin, ghrelin, and psychosocial indices at 12 and 24 months(ii)the degree of adherence to each of the support strategies over the 24 months(iii)the degree of adherence to each of the diet (Mediterranean, intermittent fasting, modified Paleo) and exercise (current recommendations, HIIT) plans that are selected over the 24 months and the outcomes within these self-selected groups.

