### Choice of diet and exercise plan

If a participant is eligible and has completed all baseline assessments, they will be provided with information on each of the possible three dietary and two exercise approaches, and allowed to choose which might suit them best.

Their choice of dietary approaches will be:*Mediterranean* – High amounts of fruit, vegetables and wholegrain cereals, moderate amounts of protein (particularly from fish), nuts (up to 30 g per day), olive oil and dairy foods, and limited amounts of processed and sugary foods. Calorie counting will not be required (unless randomised to MyFitnessPal), but energy intake should be reduced by appropriate levels through promotion of appropriate foods and serving sizes.*Modified paleolithic* – Strict paleolithic diets remove all processed and cereal-based foods, legumes and dairy products which we believe is not sustainable for most overweight people long-term. Participants who choose this diet can decide to remove these foods; but we will also suggest they follow an 80:20 rule where up to one serving of dairy products, legumes and appropriate low glycaemic index, wholegrain carbohydrates are allowed each day. We believe this still fits the paleolithic philosophy while promoting greater long-term adherence through flexibility. Calorie counting will not be required (unless randomised to MyFitnessPal), but energy intake should be reduced by appropriate levels through promotion of appropriate foods and serving sizes.*Intermittent fasting (5:2 plan)* – Participants choose two days per week (any days, not consecutive, can vary from week to week to fit lifestyle) where energy intake cannot exceed 2 (females) – 2.5 (males) MJ. In practice, this usually means a small breakfast (e.g. plain porridge), no or limited food during the day, and non-starchy vegetables only for the evening meal, although other variations are possible. Participants can eat *ad libitum* on the remaining days.

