### Randomisation

Once participants have chosen their diet and exercise approach, randomisation will occur using sequentially numbered opaque sealed envelopes prepared by the statistician. The participants will be stratified by sex and random length blocks will be used to allocate the treatment. Participants will then be booked into their first intervention session.

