### Intervention groups and sessions

*Control* – those randomised to the control condition will meet with research staff to discuss which diet and exercise options would suit them best. They will also receive the resource detailing the evidence-based behavioural weight loss strategies noted above. They will then be left to their own devices for the remainder of the study (except for attending all outcome assessments).*Regular brief support* – Participants in this group will attend an appointment at the study clinic once a month to be weighed. During this time they will have the opportunity for a 5–10 minute conversation with research staff to assess progress, review and brainstorm solutions to problems if any exist, and encourage adherence. These sessions are modelled on our successful *HEAT* study and provide an opportunity for support and ongoing assistance with strategies [22].*App* – Participants in the app group will attend an appointment to learn how to use MyFitnessPal to monitor their energy and macronutrient intakes. They will be provided with assistance in setting up their MyFitnessPal account to be compatible with their chosen diet, and will be shown how to use the app on their smartphone and/or computer. Participants will be asked to monitor their dietary intake every day for the first month, and for one week of every month for months 2–12.*Daily self-weighing* – Individuals randomised to this group will receive instruction and support about weighing themselves every day (same time of day and degree of clothing). Participants will text their weight or enter it online using a web page connected to our secure database each day which will have a graphical display. Progress and adherence to entering/sending weight data will be checked every week and reminder texts sent where necessary. Every month, research staff will provide personalised progress feedback and support by email.*Biochemical hunger training* – This group will follow a 4-week protocol that trains them to recognise “real” (biochemical) hunger by associating feelings of hunger with blood glucose levels following fingerprick testing with portable glucometers. Our protocol is based on that of Ciampolini et al. [45] but adapted slightly following piloting. In the original method, participants are only able to eat if blood glucose is less than 4.7 mmol/L [45]. Our pilot testing showed that use of an individualised blood glucose cut-off (average of fasting blood glucose over two days) rather than 4.7 mmol/L improved adherence to testing and reduced eating when blood glucose was not below the cut-off [78]. Before every desired eating occasion, participants will be instructed to note their intensity of hunger on a 100mm visual analogue scale and their measured blood glucose. If their blood glucose is higher than their personal cut-off, they are advised to engage in some other activity as a distraction and wait at least one hour. At this time, they assess their feelings of hunger again and repeat the measurement if they still want to eat, until their blood glucose is under their individualised cut-off. Over time, participants learn to relate physical feelings of hunger with their blood glucose and to eat only when physically hungry. Participants will be advised to follow this procedure for two weeks. In weeks 3 and 4, the blood glucose testing is optional, but all other recording (intensity and type of hunger, and resulting food intake) continues. Participants will be in regular contact with support staff, who will advise them how to proceed, answer any queries and provide encouragement. In months 2–12, participants will be advised to repeat the recording process (with or without fingerprick blood glucose testing) for one week of every month.

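### The goal sentence promises to determine whether choice of diet and exercise plan improves adherence and weight loss, but every participant chooses, so an effect of choice cannot be estimated

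*Protocol article*

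**What the plan says.** All references are to the protocol article.

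- **Aims and objectives, first sentence.** The stated goal is to "determine whether allowing participants to choose from a selection of appropriate diet and exercise plans", placed in the setting of a randomised trial of four support strategies, "enhances adherence and promotes greater weight loss and positive health outcomes".
- **Background.** The paragraph on choice ends with a call that begins "Thus further examination of the impact of being able to" and goes on to choosing a diet or activity plan.
- **Choice of diet and exercise plan.** Eligible participants who have completed baseline are "provided with information on each of the possible three dietary and two exercise approaches, and allowed to choose which might suit them best".
- **Randomisation.** "Once participants have chosen their diet and exercise approach, randomisation will occur using sequentially numbered opaque sealed envelopes".
- **Control arm, under Intervention groups and sessions.** The text reads: "those randomised to the control condition will meet with research staff to discuss which diet and exercise options would suit them best".
- **Aims and objectives, second paragraph.** The primary aim is the effect of the support strategies on weight loss at 12 and 24 months. Secondary aims (i) and (ii) concern effects of, and adherence to, those strategies. Secondary aim (iii) concerns adherence to the plans that participants select, and outcomes within those self-selected groups.
- **Statistical analyses and power calculations.** Three analyses are described: the RCT analysis by support strategy, a cross-sectional analysis of who picks which plan, and a cohort analysis of adherence by chosen plan and its relation to outcomes.

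**The concern.** In the goal sentence the exposure is being allowed to choose, and the support-strategy trial is only the setting. To determine whether choice helps, some participants would have to be given a plan without choosing it, or a stated outside group would have to stand in for them. The article describes neither.

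What is at stake is interpretation. If adherence or weight loss turns out well, the goal as worded invites the reader to credit choice, with no comparison behind the claim. The direction cannot be taken for granted. The Background itself says that the few existing studies mostly do not bear out the theory that choice helps, and that one found greater weight loss in people randomised to a diet than in people who chose theirs.

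**Working it through.** The goal has no figure of its own to reproduce, so the check is whether the effect it names can be identified from the design.

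**1. What the sample size refers to.** The article gives 42 per group for 90 % power to detect a 4 kg difference between any pair of support groups, then allows for 15 % loss: 42 / (1 − 0.15) = 49.4, rounded up to 50, and 5 × 50 = 250. The 42 is reproduced if one assumes a baseline-adjusted comparison of the mean of two follow-up weights: SD = 15 × √((1 + 0.9)/2 − 0.9²) = 15 × √0.14 = 5.61 kg, giving 42. The article does not state the number of follow-ups. With one to three follow-ups, and adjusted or change-score analysis, the requirement runs from 37 to 60. Whichever applies, the calculation is for support groups. No power is claimed for choice.

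**2. How choice varies across the trial.**

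| Arm | Planned n | Chose a plan | Did not choose |
|---|---|---|---|
| Control | 50 | 50 | 0 |
| Brief support | 50 | 50 | 0 |
| App | 50 | 50 | 0 |
| Daily self-weighing | 50 | 50 | 0 |
| Hunger training | 50 | 50 | 0 |
| Total | 250 | 250 | 0 |

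The control description places a discussion of options after allocation, whereas the Randomisation section places the choice before it. On either reading, controls choose.

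**3. Identifiability.** Let A₁ to A₄ indicate the four active arms and C indicate having been given a choice:

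E(Y) = β₀ + β₁A₁ + β₂A₂ + β₃A₃ + β₄A₄ + γC

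Because C = 1 for everyone, its column is identical to the intercept. The design matrix without C has 5 columns and rank 5. With C it has 6 columns and still rank 5. Only the sum β₀ + γ is estimable, so γ is not, and more participants would not change that. The arm effects β₁ to β₄ remain estimable.

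**4. Whether any planned analysis supplies the missing contrast.**

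- RCT analysis: compares support strategies among people who all chose.
- Cross-sectional analysis: describes the popularity of plans and the characteristics of those who pick them.
- Cohort analysis and secondary aim (iii): compare or describe groups defined by chosen plan (three diets, two exercise options). Every group consists of choosers, and membership is self-selected.

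None sets choosing against not choosing.

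**The case against.** The strongest reply is that too much is being read into one introductory sentence. The next paragraph lists the aims, and none asks about choice versus no choice. The Study design section and the primary analysis concern support strategies. In the Abstract's discussion and the main Discussion, choice is something the authors believe will help, and the Aims section itself goes on to call the improvement expected. The Abstract already frames the trial as comparing ways of supporting people on a plan of their choice. No conclusion crediting choice is announced, and the cohort analysis is kept apart from the randomised one.

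Most of this stands, and it limits the point. A reader might infer that the trial's design or its main question is unsound. The documents do not support that: choice is held constant across arms and is made before allocation, so it does not disturb the randomised contrasts. A reader might also infer that the Background shows randomised evidence against choice. It says less: the question has been studied infrequently, the findings in general do not favour the theory, and many of the studies were small and imprecise or, in one case, shorter than a year. Most of those described concern having a preference.

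What the reply does not remove is the contradiction. The same section presents the benefit of choice as something to be determined and, two sentences later, as an expectation. The Background's call for further study reinforces the first reading. A separate analysis plan could not cure this, because no analysis creates a contrast that the design lacks.

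**Conclusion.** The concern holds for the goal sentence and its Background motivation. With 250 of 250 planned participants choosing and none assigned a plan, the effect of choice on adherence, weight or health cannot be estimated. This rests on the article's account that every eligible participant chooses, and on its describing no external group of people assigned a plan.

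It does not extend to the listed aims, the randomised comparison of support strategies, the primary analysis or the sample size. The count of 250 to 0 shows that the contrast is absent; it does not measure a bias in any planned result. This is a should-fix: the stated goal is wrong as written and bears on what may be concluded, but the trial can answer its primary aim as designed.

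**What to change.** 1. Reword the opening sentence of Aims and objectives to agree with the primary aim and with the Abstract's discussion: the goal is to compare four support strategies with control among adults who follow a self-chosen diet and exercise plan.
2. Present the expected benefit of choice as a rationale and an assumption, not as something the study will determine. Adjust the closing call in the Background's paragraph on choice so that it does not imply that this trial supplies the missing test.
3. State that adherence and outcomes by chosen plan, in secondary aim (iii) and the cohort analysis, are observational, and that no conclusion about choice versus assignment will be drawn from them.

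The cost is a few sentences. Arms, recruitment, randomisation, assessments, sample size and primary analysis stay as they are. Keeping the goal as worded would instead require a comparator without choice, which is a different and larger trial.
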